#### Multivariate Analyses:

We will conduct secondary/advanced analyses by specifying multivariate and longitudinal regression models of the primary and secondary outcome measures, in order to estimate treatment differences adjusted by potential confounders, and to explore individual and group trajectories using available repeated measures data. Final analyses will include multi-level linear mixed-effect models and generalized linear and latent mixed models (GLLAMM) of the primary and secondary outcome measures by combining the data across all time points depending on the measurement scale of the dependent variables. We will include variables such as age, gender, race/ethnicity, education, income, diagnosis and severity in these models as confounders or moderators or control variables. The statistical evaluation of the coefficient estimate for the MBSR intervention indicator (average difference between the groups across all time points) will be based on both the confidence interval and p-value approaches described earlier (see Outcome Assessment) to assess the non-inferiority hypothesis in the context of generalized linear mixed effect models.

For secondary outcomes, data will be summarized using descriptive statistics such as means and standard deviations and frequencies and percentages for the overall sample and by treatment groups. Group differences will be first tested using bivariate statistics like t-tests and chi-square tests as appropriate. Secondary/advanced analyses will be conducted by specifying multivariable longitudinal regression models of the secondary outcome measures in order to estimate treatment differences at each time point while adjusting by potential confounders, and to explore individual and group trajectories using available repeated measures data. Linear mixed models will be adjusted for sex, age, race, anxiety severity at baseline (low vs high) and site, including time and treatment indicators and their interactions and estimated with random effects at participant level.

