| Sleep ( PSQI, PROMIS-sleep anxiety measure )                    |        | ✖                         |        |        | ✖      |        | ✖                      |                    | ✖                  |
| Quality of Life/Functioning                                     |        | ✖                         |        |        | ✖      |        | ✖                      | ✖                  | ✖                  |

|                                                          |   |    |   |   |   |   |   |   |   |
|----------------------------------------------------------|---|----|---|---|---|---|---|---|---|
| (PROMIS- SPSR and PROMIS- APSRA-8)                       |   |    |   |   |   |   |   |   |   |
| Adverse Experiences (CTQ and LEC)                        | ✖ |    |   |   |   |   |   |   |   |
| Work performance (HPQ)                                   |   | ✖  |   |   |   |   |   |   | ✖ |
| Clinician-rated assessments of outcome                   |   |    |   |   |   |   |   |   |   |
| Psychiatric Diagnoses (MINI)                             | ✖ |    |   |   |   |   |   |   |   |
| Anxiety symptom severity (CGI-S /CGI-I)                  |   | ✖  |   |   | ✖ |   | ✖ | ✖ | ✖ |
| Disorder-specific scales (PDSS, SIGH-A, LSAS)            |   | ✖  |   |   | ✖ |   | ✖ | ✖ | ✖ |
| Measures of Safety and Study Integrity                   |   |    |   |   |   |   |   |   |   |
| Side Effects (FIBSER & Adverse Events)                   |   |    | ✖ | ✖ | ✖ | ✖ | ✖ | ✖ | ✖ |
| Adherence/ Homework                                      |   |    | ✖ | ✖ | ✖ | ✖ | ✖ | ✖ | ✖ |
| Depressive symptoms (QIDS-SR including suicidality item) |   | ✖  |   |   | ✖ |   | ✖ | ✖ |   |
| Vital Signs                                              | ✖ |    |   |   | ✖ |   | ✖ |   |   |
| Clinician Suicide Assessment                             | ✖ | ✖* | ✖ | ✖ | ✖ | ✖ | ✖ | ✖ | ✖ |
| Concomitant Treatment                                    | ✖ | ✖* | ✖ | ✖ | ✖ | ✖ | ✖ | ✖ | ✖ |
| Weight                                                   | ✖ |    |   |   | ✖ |   | ✖ |   |   |
| Blood draw, ECG, Urine pregnancy/drug test**             | ✖ |    |   |   |   |   |   |   |   |

\*these measures will be repeated with MD/NP during first week of treatment (referred to as “week 0”) unless the participant has been randomized to MBSR *and* less than two weeks elapse between that participant’s baseline visit and the start of their treatment)

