#### Escitalopram (ESC)

During the 8 weeks of randomized treatment with ESC, subjects will be seen at baseline, post-baseline medication pick-up visit, weeks 1, 2, 4, 6, and 8 week endpoint, and at 12 week follow-up, (9 visits total) by a study physician/nurse practitioner. Georgetown University Medical Center's research pharmacy will be responsible for preparing the medication, which will be given to the participants by a study M.D. from baseline to week 12. Patients will take the pills each day at home. ESC will be initiated at 10 mg/day; which will be continued to week 2, when it will be increased to 20mg/day if well tolerated (or delayed if not). Medication adherence will be assessed by pill count and a standardized adherence measurement [68]. Side effects will be assessed at each visit and recorded. Participants will also be instructed to contact study staff immediately if any significant side effects, symptomatic worsening, or suicidal ideation develops in between visits. After week 12, if the patient desires to stay on the medication, s/he will be given a prescription by the study MD/NP., who will also start the process of transition to outpatient care so that the patient can continue treatment after the end of the study, if desired.

If in-person visits are not possible for any reason (e.g., coronavirus), the study medication will be shipped directly to the patient from the research pharmacy following the pharmacy protocols and the study visits will be conducted using telehealth videoconferencing or telephone contact.

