### Outcome Assessment:

The treatment response (CGI-I) will be compared by groups and tested via confidence intervals to examine the precision of non-inferiority. A review of methods for non-inferiority studies on behavioral treatments (Steinert et al 2017) found that of the eight published studies reviewed, the effect size used in the non-inferiority margin calculation ranged between  $d=0.26$  and  $d=0.6$ . One of the examples in this review was a study of CBT that included all anxiety disorders,

similar to the sample in our current proposal (Norton and Barrera 2012). For this study, the researchers also surveyed the literature to determine the best way to calculate a non-inferiority margin with a transdiagnostic sample. They proposed that the non-inferiority margin be computed by multiplying the standard deviation of the particular outcome measure by the meta-analytically derived effect size, deriving their approach from a standard methodology recommended for rigorous equivalence designs (e.g. see Jones et al 1996). Using this calculation method, and using the SD of 1.1 points for CGI change scores from other escitalopram trials across anxiety disorders (see summary in Bandelow et al 2006), would have yielded a non-inferiority margin of 0.66 unit on the CGI-S (by multiplying 1.1 by 0.6). However, to be more conservative, a non-inferiority margin of 0.33 ( $0.3 \times 1.1$ ) was used in our sample size calculations. This margin represents a difference of 1/3 of a point on the CGI-S score. We also defined a largest-clinically-acceptable non-inferiority margin following the literature by determining the halfway point between these two numbers (0.66 and 0.33) to get 0.495, ( $0.45 \times 1.1$ ) such that a difference of 0.495 or smaller will still allow us to declare MBSR to be noninferior to escitalopram treatment. Further support for the appropriateness of this margin comes from the literature where a change of 1.0 unit, substantially higher than a margin of 0.495, is considered the Minimal Clinically Important Change (MCID) score for the CGI-S and has been used to anchor definitions of clinically significant change across other measures.

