Therefore, the null hypothesis for the non-inferiority test will be that the drug group's mean CGI-S score reduction at endpoint is greater than that of the MBSR group by at least 0.495 points (for this scale, higher scores indicate higher severity and greater reduction indicated greater improvement). In other words, if the MBSR group's post-intervention mean CGI-S score change is less than that of the drug group by not more than 0.495 points we will consider MBSR to be non-inferior to the standard pharmacotherapy escitalopram. Based on these parameters, the required analysis sample size with equal allocation to achieve an 80% power at significance level of 0.05 will thus be N=276 study completers.

To conservatively address attrition, we estimate our projected dropout rate to be 25% and therefore plan to randomize 368 participants with a 1:1 ratio to each group, yielding 276 completers after drop-out. Of note, many published non-inferiority trials have relied on intent-to-treat analyses that are more liberal than our proposed completer analysis. We also propose to conduct sensitivity analyses with the intent-to-treat sample as a follow-up to our primary completer analysis.

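### The secondary mixed model tests non-inferiority on a treatment difference averaged over all visits, although the hypothesis and its 0.495 margin are set on CGI-S change at endpoint

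*Protocol*

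**What the plan says.** **Hypothesis and margin.** The Outcome Assessment section of the protocol states the null as the drug group's "mean CGI-S score reduction at endpoint is greater than that of the MBSR group by at least 0.495 points". The deciding analysis is a completer analysis, with intent-to-treat as sensitivity.

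**Mixed model.** The Multivariate Analyses section introduces secondary/advanced longitudinal models of the primary and secondary outcomes, then describes final analyses that pool data from all time points. For these it takes the "coefficient estimate for the MBSR intervention indicator (average difference between the groups across all time points" and evaluates it by the confidence-interval and p-value approach of the Outcome Assessment section, expressly to assess the non-inferiority hypothesis.

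**Visits.** The Table of Assessments row "Anxiety symptom severity (CGI-S /CGI-I" marks five visits: baseline, week 4, primary endpoint, week 12 and week 24. The Multivariate Analyses section does not exclude any of them.

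**Treatment after week 8.** The MBSR course lasts eight weeks. Escitalopram is "given to the participants by a study M.D. from baseline to week 12", and may continue by prescription after that.

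**Secondary outcomes.** A separate paragraph plans differences at each time point, from models "including time and treatment indicators and their interactions and estimated with random effects at participant level".

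**The concern.** One hypothesis and one margin are applied to two different quantities. The margin of 0.495 was justified for a difference in change at the end of treatment. An average over five visits also takes in baseline, where randomisation makes the expected difference zero, a mid-treatment visit, and two visits after the randomised treatment period. Nothing in the protocol justifies 0.495 as a margin for that average.

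In a superiority trial, averaging in a visit with no difference costs power. In a non-inferiority trial it moves the estimate towards the conclusion the trial hopes to reach. At stake is a second, model-based statement of non-inferiority that would be read as support for the primary result while its error rate at the week-8 margin is not the nominal one.

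**Working it through.** **Inputs from the protocol (Outcome Assessment).** The SD comes from "using the SD of 1.1 points for CGI change scores from other escitalopram trials across anxiety disorders". The sample-size margin is described as "to be more conservative, a non-inferiority margin of 0.33". The test is planned to "achieve an 80% power at significance level of 0.05". The decision margin is 0.495.

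**The plan's own figure.** n per arm = 2 × (1.645 + 0.842)² × 1.1² / 0.33² = 137.4, rounded up to 138. That gives 276 completers, and 276 / 0.75 = 368 randomised. Both stated figures reproduce with one-sided 0.05; one-sided 0.025 would give 350 completers. I therefore use one-sided 0.05 and 138 per arm.

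**What the coefficient estimates.** In a balanced random-intercept model with a treatment main effect and no interaction, the treatment coefficient is the simple mean of the visit-specific differences.

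**Assumptions, not in the protocol.**
- Equal correlation ρ between visits, from 0.3 to 0.7.
- Complete data for 138 per arm.
- The deficit profiles in the table below.

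Because 1.1 is the SD of a change score, the per-visit SD is 1.1 / √(2(1 − ρ)), that is 0.93, 1.10 and 1.42 at ρ = 0.3, 0.5 and 0.7.

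**Formulas.** For k visits, SE = SD per visit × √[(1 + (k − 1)ρ)/k] × √(2/138). With a true week-8 deficit exactly at the margin, P(non-inferiority declared) = Φ[(0.495 − averaged deficit)/SE − 1.645]. For a week-8 change-score contrast, SE = 1.1 × √(2/138) = 0.132 and the rate is 5% by construction.

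**All five visits as outcome rows.** At ρ = 0.5, SE = 1.1 × √(3/5) × √(2/138) = 0.1026.

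| Deficit as a multiple of week 8 (baseline, 4, 8, 12, 24) | Averaged deficit | Rate at ρ = 0.5 | Rate for ρ = 0.7 to 0.3 |
|---|---|---|---|
| 0, 1, 1, 1, 1 | 0.80 × 0.495 = 0.396 | 25% | 16% to 38% |
| 0, ½, 1, 1, 1 | 0.70 × 0.495 = 0.347 | 42% | 26% to 64% |
| 0, ½, 1, 1½, 1½ | 0.90 × 0.495 = 0.446 | 12% | 10% to 16% |
| 0, 1, 1, 1½, 1½ | 1.00 × 0.495 = 0.495 | 5% | 5% |

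First row worked: (0.495 − 0.396)/0.1026 − 1.645 = −0.680, and Φ(−0.680) = 0.25.

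The five-visit average is below the week-8 deficit d whenever the week 4, 12 and 24 deficits sum to less than 4d, that is, unless they average at least 4/3 of d.

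**Post-baseline visits only**, no baseline adjustment, ρ = 0.5: SE = 1.1 × √(2.5/4) × √(2/138) = 0.1047.

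| Multiple of week 8 (4, 8, 12, 24) | Averaged deficit | Rate |
|---|---|---|
| 1, 1, 1, 1 | 0.495 | 5% |
| ½, 1, 1, 1 | 0.433 | 15% |
| ½, 1, ⅔, ⅓ | 0.309 | 55% |
| ½, 1, 1½, 1½ | 0.557 | about 1% |

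Adjusting for baseline replaces (1 + 3ρ)/4 by (1 + 3ρ)/4 − ρ², so SE falls to 0.081. The constant-deficit rate stays at 5% and the other rates move further from 5%: the second row becomes 19%.

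**The case against.** The strongest reply is that this is not the deciding test. The models are labelled secondary/advanced, and the Outcome Assessment section rests the decision on the completer analysis at endpoint. That stands. A reader might take the 25% or 42% as the trial's false-positive risk; the protocol does not support that, because these rates belong to the supporting model alone.

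A second reply concerns direction. A reader might infer that averaging always pulls the deficit towards zero because the follow-up visits are off treatment. That is wrong for escitalopram, which is supplied to week 12 and may continue. Only the MBSR course has ended, so a deficit could widen after week 8 as well as fade, and the calculation shows an average equal to or above the week-8 deficit under some profiles. Only a baseline row dilutes with certainty.

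Third, counting baseline as an outcome row is itself a reading. Pooling all time points points that way, but the endpoint is a change score and severity is listed as a possible control variable. If baseline is only a covariate, a constant deficit gives exactly 5%.

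Fourth, one might argue that with treatment-by-time interactions and baseline as reference, the treatment coefficient is merely the baseline difference and would meet the margin whatever the treatments do. The interaction model is written for secondary outcomes, and for the non-inferiority test the protocol defines the coefficient as an average. That charge does not hold.

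None of these replies removes the mismatch: the text assigns the endpoint hypothesis to an all-visit average.

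**Conclusion.** The point holds as a should-fix. The secondary mixed model of CGI-S assesses the endpoint hypothesis on a quantity that is not the endpoint difference. The primary completer test is untouched.

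With baseline as an outcome row and a deficit constant afterwards, the false non-inferiority rate at the margin is about 25% at correlation 0.5, five times nominal. It is 42% if only half the deficit has appeared by week 4. Without a baseline row the sign of the error is not determined: the rate runs from about 1% for a widening deficit, through 5% for a constant one, to 55% for one that fades to a third by week 24. These figures rest on assumed deficit profiles and correlations, complete data for 138 per arm, a change SD of 1.1 and one-sided 0.05. The mismatch itself needs none of those assumptions.

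**What to change.** Replace the sentence on the averaged coefficient with wording such as: in the mixed model, non-inferiority is assessed against 0.495 on the MBSR minus escitalopram contrast at week 8, from a model with post-baseline CGI-S as outcome, baseline CGI-S as covariate, and treatment, visit and treatment-by-visit terms. Report weeks 4, 12 and 24 as separate contrasts, and do not apply the week-8 margin to an average over visits. The protocol already plans visit-specific differences for the secondary outcomes, so no new machinery is needed.

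The cost is a wording change, one contrast statement and a somewhat wider interval. At correlation 0.5 the baseline-adjusted week-8 contrast has SE 1.1 × √(1 − 0.25) × √(2/138) = 0.115, against 0.081 for the baseline-adjusted four-visit average.

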#### **IV. SPECIFIC AIMS (Research Objectives)**

We will assess the comparative effectiveness of Mindfulness-Based Stress Reduction (MBSR) compared to escitalopram (ESC) for patients with anxiety disorders (generalized anxiety disorder, panic disorder, agoraphobia, and social anxiety disorder), by randomizing patients to eight weeks of (1) MBSR or (2), flexible-dose escitalopram. This two-arm, three-site, randomized, controlled study will use a standard non-inferiority study design which incorporates previous data demonstrating that escitalopram is an effective treatment for anxiety and has been proven against pill placebo. Based on non-inferiority driven power calculations (see Analysis plan), we plan to randomize 368 patients to either MBSR or medication. We expect that 276 will complete the protocol after 25% dropout; however treatment satisfaction including dropout and intent-to-treatment outcomes will also be important assessments to guide conclusions about patient preferences and treatment responses. This non-inferiority randomized design with standardized blinded assessments provides the most rigorous comparison data regarding comparison of the novel treatment of MBSR to a gold standard treatment, escitalopram. This study will provide crucial information to patients about effective and acceptable treatment strategies for anxiety.

We will examine several secondary outcome measures and exploratory outcomes. Overall Anxiety Severity and Impairment Scale (OASIS) is the secondary measure of anxiety symptoms. To assess satisfaction/acceptability of treatment, we will use the Client Satisfaction Questionnaire (CSQ) and the Reactions to Treatment Questionnaire (RTQ). To assess sleep outcomes, we will use the Pittsburgh Sleep Quality Index (PSQI), The Beck Anxiety Inventory (BAI) is a 21-item self-report inventory designed to measure severity of anxiety symptoms in

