### Clinician-Rated Outcomes

The primary measure of anxiety symptoms is the **Clinician Global Impression-Severity Scale (CGI-S)**. Additionally, we will utilize the **Clinical Global Impression-Improvement (CGI-I)** Scale [45-48]. The CGI has excellent psychometric properties, is treatment sensitive, and highly correlated with anxiety and depression scales across disorders [49].

The **MINI International Neuropsychiatric Interview** **MINI** will be administered by a trained interviewer, and will take approximately 25 minutes. This short, diagnostic structured interview

has proven to provide reliable diagnoses (Lecrubier et al., 1997) and is considerably shorter than other structured diagnostic interview tools.

The **Structured Interview Guide for the Hamilton Anxiety Scale (SIGH-A)** is designed to assist clinicians in evaluating anxiety symptoms through the HAM-A. The 14-item HAM-A (Hamilton 1959) was developed to assess general anxiety symptoms in a clinical population and has proven sensitive to change with treatment. The SIGH-A provides specific and detailed rating guidelines for the purposes of administering and scoring the HAM-A, and has demonstrated high interrater and test-retest reliability [59].

The **Panic Disorder Severity Scale (PDSS)** is a semi-structured interview of panic symptom severity. It contains 7 items assessing multiple dimensions of PD severity, including a) frequency of panic attacks, b) distress during panic attacks, c) anticipatory anxiety, d) agoraphobic fear and avoidance, e) interoceptive fear and avoidance, f) impairment of work and social functioning. The PDSS is a widely applied measure of the severity of panic disorder symptoms [58].

The **Liebowitz Social Anxiety Scale (LSAS)** is a reliable and validated measure of social anxiety, that assesses both fear and anxiety about common social situations, as well as avoidance components of social anxiety [60].

The **Frequency, Intensity, and Burden of Side Effects Ratings (FIBSER)** is a 3-item, validated measure to assess the frequency, intensity, and interference of side effects due to study treatment. The **Adverse Events Form** is a form for the study clinician to fill out while interviewing patient which lists all adverse events and side effects due to study treatment.

The **Concomitant Treatment Form** is a form for the study clinician to fill out while interviewing patient which indicates forms of treatment that the patient may have started or stopped.

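### Site is named as a model term only in the secondary-outcome paragraph; it should also enter the primary CGI-S comparison, and the two unmatched covariate lists should become one fixed set

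*Protocol*

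**What the plan says.** Section IV (Specific Aims) describes the trial as "This two-arm, three-site, randomized, controlled study". Three places in section VIII bear on adjustment.

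- **Outcome Assessment.** The primary null hypothesis is that "the drug group's mean CGI-S score reduction at endpoint is greater than that of the MBSR group by at least 0.495 points". It is to be tested in completers by confidence interval. No covariate and no site term is named.
- **Multivariate Analyses, first paragraph.** This plans "multivariate and longitudinal regression models of the primary and secondary outcome measures" and labels them secondary or advanced. On covariates it says: "We will include variables such as age, gender, race/ethnicity, education, income, diagnosis and severity in these models as confounders or moderators or control variables". The treatment coefficient is the "average difference between the groups across all time points", and it too is to be used to assess non-inferiority.
- **Multivariate Analyses, second paragraph.** This opens with the secondary outcomes and plans models that estimate the treatment difference at each time point. It closes with a definite list: "Linear mixed models will be adjusted for sex, age, race, anxiety severity at baseline (low vs high) and site". This is the only place in the protocol where site is named as a model term.

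The protocol text shown does not mention stratifying randomization by site.

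**The concern.** Site is a basic design factor of a multicentre trial. The protocol judges it worth adjusting for, but says so only for the secondary outcomes. If the primary comparison is run as described, differences between sites in case mix or class delivery stay in its error term. The primary analysis set is completers, with 25% dropout expected, so randomization alone does not guarantee that the arms keep the same site mix in the data analysed.

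The second issue is specification. Each secondary outcome is covered by two paragraphs with different covariates and different target effects, and nothing says which result is the main one. The first paragraph also leaves open whether a variable enters as a confounder, a moderator or a control. A moderator normally brings an interaction with treatment, which changes what the treatment coefficient means, and that coefficient is to carry a non-inferiority statement.

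**Working it through.** **1. The plan's own figure.** Inputs from Outcome Assessment: SD of CGI change 1.1, sample-size margin 0.33, power 80%, significance level 0.05 (sidedness not stated), 1:1 allocation, 25% dropout. With a true difference of zero and a one-sided 0.05 level:

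n per arm = 2 × 1.1² × (1.645 + 0.842)² / 0.33² ≈ 137.4, rounded up to 138. The total is 276, and 276 / 0.75 = 368.

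Both stated figures reproduce exactly. The formula has no site or covariate term.

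**2. The two covariate lists side by side.**

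| Item | First paragraph | Second paragraph |
|---|---|---|
| Outcomes | primary and secondary | secondary |
| Type of list | open (examples) | closed |
| In both | age, gender, race/ethnicity, severity | age, sex, race, severity (low vs high) |
| Only here | education, income, diagnosis | site |
| Target effect | average over all time points | difference at each time point |

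**3. What adjusting for site could gain.** The protocol gives no site variance. Assume site explains a share R² of the variance of CGI-S change. The standard error is then multiplied by √(1 − R²), and 276 completers are worth 276 / (1 − R²). Power is at 138 per arm, margin 0.33, one-sided 0.05.

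| R² (assumed) | Residual SD | SE reduction | 276 is worth | Power |
|---|---|---|---|---|
| 0 | 1.100 | 0% | 276 | 80.2% |
| 0.02 | 1.089 | 1.0% | 282 | 80.9% |
| 0.05 | 1.072 | 2.5% | 291 | 81.9% |
| 0.10 | 1.044 | 5.1% | 307 | 83.7% |

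**4. What an imbalance in site mix could do.** Shift in the unadjusted difference = (difference in mean change between one site and the others) × (difference in that site's share between arms). Both factors are assumed:

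- Low end: 0.3 × 0.03 = 0.009, which is 2% of the 0.495 decision margin.
- High end: 0.7 × 0.10 = 0.07, which is 14% of that margin.

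For scale, assume equal-sized sites and no stratification. The chance SD of the difference in one site's share, with 138 completers per arm, is √(2 × 1/3 × 2/3 / 138) = 0.057. Differences of 3 to 10 percentage points are then about 0.5 to 1.8 SDs.

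**5. Type I error.** If randomization were stratified by site (not stated), leaving site out of the analysis would be slightly conservative. At R² = 0.10, the true one-sided error at a nominal 0.05 is 1 − Φ(1.645 / √0.90) ≈ 0.042.

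**The case against.** The strongest reply is that the covariates of a primary model are commonly left to the SAP, which is not at hand. Outcome Assessment sets out hypothesis, margin and sample size; it does not exclude site. That stands: silence there is not an error, and the site term for the primary test is a recommendation. It is still reasonable to make, because the protocol labels its adjusted models as secondary or advanced, so the primary test reads as an unadjusted comparison.

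A reader might infer that the first list shuts site out of the primary-outcome models. It does not, because it offers examples. The sentence that names site also refers to linear mixed models without restriction. Only its paragraph ties it to secondary outcomes, so it may be meant for the primary-outcome mixed models too. If so, the text should say so.

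A reader might infer that each secondary outcome has two incompatible models. That is too strong. A model could satisfy the closed list and also carry variables from the open one, and the two paragraphs aim at different effects. What remains is a mismatch, with no statement of which estimate leads.

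A reader might point to evaluators who differ by site. Section VII weakens this: evaluators share training and supervision across sites and may rate patients from any site. Differences in case mix and class delivery remain possible.

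Finally, every magnitude above is assumed. The 0.07 shift needs both inputs at the top of their ranges at once. Chance imbalance is also not systematic bias; only dropout that differs by both arm and site could produce that.

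**Conclusion.** The point holds as a modest improvement in specification and precision. Site is named only for the secondary outcomes, the list covering the primary outcome is open and does not name it, and the secondary outcomes fall under two lists that do not match in covariates or target effect.

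The size rests on an assumed site share of 2% to 10% of the variance of CGI-S change, which gives a standard error about 1% to 5% smaller. The possible shift from site imbalance, about 0.01 to 0.07 points, is likewise an illustration and not an estimate of bias. The documents do not support a claim that the primary analysis is invalid or that the trial is too small: 276 and 368 stand without a site term, and adding one can only help under these assumptions.

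**What to change.** - Include site as a fixed effect in the primary CGI-S non-inferiority comparison and in the mixed models of the primary outcome.
- Replace the two lists under Multivariate Analyses with one fixed adjustment set that includes site, applied to primary and secondary outcomes, and state the form in which baseline severity enters.
- List moderators separately, so that the treatment coefficient used for non-inferiority comes from a model without treatment interactions of that kind.
- State which secondary-outcome estimate is the main one: the average over time points, or the difference at a named time point.

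The cost is a change of wording and two degrees of freedom (three sites minus one). No new data are needed, since site is known for every participant, and the sample size need not change.

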### Treatments

#### Mindfulness-Based Stress Reduction (MBSR)

MBSR is an 8-week group-based course developed by Jon Kabat-Zinn (1990) and colleagues at the University of Massachusetts' Center for Mindfulness. Weekly 2.5-hour long classes are given once a week, as well as one day-long weekend class during the 6th week. The classes instruct participants in the theory and practice of several forms of mindfulness meditation: a body scan (bringing awareness through the body systematically); breathing awareness (attention focused on the breath and other physical sensations); and mindfulness stretching exercises designed to bring awareness of the body and current experience of movement. Didactic teaching of the theory of mindfulness and experiential practice are both utilized during weekly classes and at-home CD-guided practice sessions.

If the MBSR course is canceled mid-way through, or is converted to an online platform for any reason (e.g., coronavirus), participants will be permitted to enroll in the online version of MBSR, or will be enrolled in a later course to finish their treatment.

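### MBSR is taught in classes, but neither the sample size nor the primary comparison allows for class; if outcomes correlate within class, the non-inferiority confidence interval is too narrow

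*Protocol*

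**What the plan says.** The Mindfulness-Based Stress Reduction section states that "MBSR is an 8-week group-based course" and that "Weekly 2.5-hour long classes are given once a week", with one further day-long class. The Escitalopram section has patients seen at scheduled visits "by a study physician/nurse practitioner". One arm is therefore grouped by class and the other is treated patient by patient, which is a partially nested design.

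The Outcome Assessment section sets the sample size "using the SD of 1.1 points for CGI change scores from other escitalopram trials across anxiety disorders" and "a non-inferiority margin of 0.33". It gives "the required analysis sample size with equal allocation to achieve an 80% power" at a significance level of 0.05 as 276 completers, or 368 randomized after 25% dropout. The decision rule uses a different margin, "such that a difference of 0.495 or smaller will still allow us to declare MBSR to be noninferior to escitalopram treatment". The primary comparison of CGI change is by confidence interval, and no variance model is described. No class size, ICC or design effect appears.

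The Multivariate Analyses section describes the longitudinal models of primary and secondary outcomes as multi-level without naming the levels. Its later paragraph on secondary outcomes names one level: those models are "estimated with random effects at participant level", with site among the adjustment variables. Class and instructor appear in no model.

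**The concern.** Patients in one MBSR class share an instructor, a group and a calendar period. A cancellation or a switch to online teaching, which the protocol allows for, would affect all members of a class at once. If their outcomes are correlated, the MBSR mean varies more than an independent-patient formula allows. A participant-level random effect captures correlation between repeated measures on one person and nothing between classmates. A site covariate removes differences between sites but not between classes within a site.

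The direction matters in this design. Leaving out positive class variance shortens the interval, and in a non-inferiority trial a shorter interval makes success easier to declare. The stated 0.05 level would then understate the risk of wrongly calling MBSR non-inferior.

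**Working it through.** **Inputs from the protocol (Outcome Assessment):** SD 1.1; planning margin 0.33; decision margin 0.495; 80% power; significance level 0.05 with sidedness not stated; equal allocation; 25% dropout.

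**Assumptions, not in the protocol:** m = 8 to 12 analysed trial patients per MBSR class; ICC = 0.02 to 0.10; true difference zero for power.

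**Step 1. Reproduce the plan's figure.** With one-sided 0.05, n per arm = 2 × [1.1 × (1.645 + 0.842) / 0.33]² = 137.4, rounded up to 138. The total is 276, and 276 / 0.75 = 368. Both match exactly with a design effect of 1. One-sided 0.025 would give 350, and a margin of 0.495 would give 124 or 156. The figure of 276 is therefore an independent-patient calculation at one-sided 0.05 and margin 0.33.

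**Step 2. Add clustering in the MBSR arm only.**

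- Design effect in that arm: DE = 1 + (m − 1) × ICC
- True SE / naive SE = √[(1 + DE) / 2]
- Actual one-sided error = Φ(−z × naive SE / true SE), with z = 1.645 or 1.960
- Power with a correct SE = Φ(margin / [1.1 × √((1 + DE) / 138)] − z)

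| m, ICC | DE | SE ratio | Error, nominal 5% | Error, nominal 2.5% | Power at 0.33, one-sided 5% | Power at 0.495, one-sided 5% | Power at 0.495, one-sided 2.5% |
|---|---|---|---|---|---|---|---|
| 8, 0.02 | 1.14 | 1.034 | 5.6% | 2.9% | 77.8% | 97.6% | 95.1% |
| 10, 0.05 | 1.45 | 1.107 | 6.9% | 3.8% | 72.8% | 95.8% | 92.2% |
| 12, 0.10 | 2.10 | 1.245 | 9.3% | 5.8% | 63.9% | 91.3% | 85.1% |

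Worked middle row: DE = 1 + 9 × 0.05 = 1.45; √(2.45 / 2) = 1.107; Φ(−1.645 / 1.107) = 6.9%; Φ(0.33 / [1.1 × √(2.45 / 138)] − 1.645) = 72.8%.

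**Step 3. Check by simulation.** With 138 patients per arm, a true difference at the 0.495 null and naive t-based limits (40,000 trials per case), m = 10 and ICC 0.05 gave errors of 7.0% and 3.9% for nominal 5% and 2.5%. With ICC 0 the errors were 5.0% and 2.5%, so the excess comes from the clustering.

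**Step 4. Cost in sample size.** Keeping 80% power at 0.33 with m = 10 and ICC 0.05 needs 338 completers: (1 + 1.45) × [1.1 × (1.645 + 0.842) / 0.33]² rounds up to 169 per arm. That is 451 randomized (338 / 0.75).

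**The case against.** Four points can fairly be made against this.

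- **The sentence that names the participant level concerns secondary outcomes.** The models that include the primary outcome are called multi-level, which could carry a class level, and naming the levels is commonly left to the SAP. This stands in part: a reader might infer that the protocol rules out a class term in the primary analysis, and it does not. But the sample size is calculated in this document with no allowance for class, and the participant is the only level it names.
- **The harm is conditional.** A reader might infer that the interval is certainly too narrow. That needs an ICC above zero, and the protocol gives neither ICC nor class size. At m = 8 and ICC 0.02 the effect is small.
- **The error figures depend on sidedness.** One-sided 5% is the reading that reproduces 276, but the protocol does not fix it. With a two-sided 95% interval, the first two scenarios stay below 5%, though all three exceed the nominal 2.5%.
- **Power is not clearly lost.** A reader might infer that the trial is underpowered. At the 0.495 margin on which the decision rests, 276 completers keep 85% or more in every row of the table. The Subject Selection section also gives 465 completers. At about 232 per arm, power at 0.33 (one-sided 5%) would be 93%, 90% and 83%. This objection stands for power, but a larger sample does not correct an interval computed with the wrong SE.

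**Conclusion.** The point holds in conditional form. MBSR is grouped, escitalopram is not, 276 is an independent-patient figure, and no class term is named for the primary comparison or any other model. If outcomes correlate within class, following the plan as written gives an interval that is too narrow and favours a finding of non-inferiority.

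The size rests on the assumed class sizes and ICCs: negligible at the low end, and material at an ICC of 0.05 or more, where 10 patients per class turn a nominal 5% into about 7%. The loss of power applies to the 0.33 planning margin only and is secondary. The documents do not support saying that the error rate is definitely inflated, that the trial is underpowered for its decision rule, or that the plan forbids a class effect. The missing allowance is certain; its consequence is not.

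**What to change.** - Record for each MBSR patient the class of first assignment. Attendance is already recorded (Adherence Documentation), but no class identifier is mentioned. Because a patient may move to an online or later course, the rule should state that first assignment defines the cluster.
- Include a random class effect in the MBSR arm only, with Satterthwaite or Kenward-Roger degrees of freedom, in the primary confidence-interval analysis and the longitudinal models. Treat each escitalopram patient as a cluster of one. This is a simplification, since prescribers may see several patients, and should be stated as such.
- Restate the power of 276 completers at the 0.33 margin over a stated range of class sizes and ICCs.

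The cost is one identifier, one model term, a modestly wider interval and a slightly less favourable stated power. If the class variance proves near zero, the result will barely change.
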